### Plans to promote participant retention and complete follow-up 

Pharmacy providers and nurses will make follow-up reminders via phone calls and/or short messages. For the follow-up visits that occur in the clinic, participants will be reimbursed Kenyan shillings 300 (approximately $3 USD) for transportation costs per local cost of living and guidelines from the Kenya Medical Research Institute.

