One pharmacy-delivered PrEP services model tested in these pilots entailed a nurse navigator stationed at a retail pharmacy who facilitated PrEP delivery for AGYW seeking contraception [15, 16]. In this pilot, Kenyan AGYW (*n* = 235) offered daily oral PrEP at two retail pharmacies frequently initiated (85%), planned to continue using (68%), and were willing to pay for PrEP services (69%), even when these were available for free at public clinics—suggesting sustainability of this approach [15]. Participants cited convenience, short wait times, less stigma, and high-quality counseling on PrEP and family planning services by the nurse navigators at the pharmacies as their reasons for preferring pharmacy- versus clinic-based PrEP services [17, 18].

In this cluster-randomized controlled trial (cRCT) in Kenya, we will determine the additional benefit (i.e., effect) of stationing a nurse navigator at retail pharmacies to support pharmacy-delivered PrEP services (versus pharmacy-delivered PrEP services without a nurse navigator) on PrEP initiation, persistence, and adherence among AGYW seeking contraception.

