### Trial design 

This is a two-arm, unblinded, cluster-randomized controlled trial in which 20 retail pharmacies offering standard PrEP delivery are randomized 1:1 to either receive or not receive a nurse navigator to support PrEP delivery for AGYW.

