### Intervention description 

In both arms, AGYW receive standard PrEP services at the pharmacy, which entail a pharmacy provider using a prescribing checklist to identify individuals with risk for HIV acquisition and at low risk of any drug contraindications, counsel them on PrEP adherence (per national guidelines), test for HIV, and prescribe/dispense PrEP with remote clinician oversight. All participants offered PrEP self-select either daily oral PrEP pills or the DPV-VR. All participants are provided with a study phone number to call free of charge for clarifying questions or concerns with PrEP use (Fig. 3).

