**Fig. 3 Fig3:**
[figure not shown]
PrEP pathway in randomization arms. AGYW, adolescent girls and young women; HIV, human immunodeficiency virus; PrEP, pre-exposure prophylaxis [23]

Pharmacies randomized to the nurse navigator model receive tailored support counseling in addition to standard PrEP services. Support counseling by nurse navigators provides educational messaging tailored to AGYW and actionable advice targeting PrEP persistence and adherence and/or FP topics and addresses participants’ questions related to the content at each study visit. Counseling includes adherence encouragement (IMB domain: motivation), PrEP efficacy and safety (IMB domain: information), self-efficacy for prevention of HIV, support for potential PrEP side effects, behavioral skills (tips for remembering PrEP medications, IMB domain: behavioral skills), and strategies for remembering PrEP refill schedules (Fig. 1). All participants receive PrEP adherence counseling per Kenyan national guidelines.

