### Provisions for post-trial care 

The study will prioritize the safety of the study participants as per ethical requirements. If a participant requires medical care that the study cannot provide, the study clinicians will refer participants to the appropriate services or organizations that can provide care. In cases of adverse events whether related to study participation or not, we will refer them for proper management. If a participant seroconverts while on PrEP, we will ensure they are referred to the HIV care clinic for confirmatory testing and linkage to care as per the national guidelines. The study provides comprehensive PrEP training to the pharmacy providers and nurses delivering PrEP to ensure they can continue to provide PrEP services post-trial.

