### Participant timeline 

Following written informed consent for participation, AGYW will be enrolled. Enrollment will include a detailed questionnaire, including assessment of demographic and behavioral characteristics, contraceptive history, education, marital status, income, relationship characteristics, HIV status and testing results, and clinical characteristics. Participants will be followed for 10 months, and study visits will be aligned with standard PrEP follow-up visits per national guidelines (i.e., first visit 30 days after PrEP acceptance, then every 3 months) for a total of 4 follow-up visits.

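### Study-visit reminders are assigned to care staff who, on a plain reading, differ by arm, and the rule that missing counts as failure can turn a resulting retention gap into apparent benefit

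*Protocol article*

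**What the plan says.** All places are in the protocol article.

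- **Reminders.** The section on retention and complete follow-up says: "Pharmacy providers and nurses will make follow-up reminders via phone calls and/or short messages". It gives one procedure, does not split it by arm, and leaves the choice of call or message open.
- **Arms.** Under Trial design, pharmacies are "randomized 1:1 to either receive or not receive a nurse navigator to support PrEP delivery for AGYW". Standard delivery (Intervention description) has a pharmacy provider who counsels, tests, and will "prescribe/dispense PrEP with remote clinician oversight". The abstract's discussion describes the comparator as delivery by pharmacy providers alone. No section places a nurse in a control pharmacy.
- **Intervention content.** "Pharmacies randomized to the nurse navigator model receive tailored support counseling in addition to standard PrEP services". The topics listed include "strategies for remembering PrEP refill schedules", but reminder calls or messages are not among them.
- **Visits.** Under Participant timeline, "study visits will be aligned with standard PrEP follow-up visits per national guidelines": the first at 30 days, then every 3 months, four in all.
- **Missing outcomes.** The statistical methods and the missing-data section both treat missing primary outcomes and loss to follow-up as discontinuation or non-adherence. Table 1 counts a woman with no 10-month hair sample because of early exit as non-adherent.

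**The concern.** A retention procedure should reach both arms equally, because retention decides whose outcome is observed. Here it is given to the people who deliver care, and one arm appears to have an extra person able to do it. Two consequences follow.

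1. **Attribution.** Because study visits are also PrEP visits, a visit reminder doubles as a prompt to return for PrEP. If reminding were fuller in navigator pharmacies, a real change in PrEP use could come from reminders and not from counselling, and the article does not say whether reminders belong to what is being tested.
2. **Measurement.** A woman who is not seen is scored as a failure. If the navigator arm sees more of its women, it scores more successes even when PrEP use is the same in both arms. The article calls the missing-data rule the most conservative choice. It is conservative for the level of use in each arm, but not for the difference between arms when retention is unequal.

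**Working it through.** **Step 1: does reminder staffing differ by arm?** The reminder sentence names two kinds of staff. Pharmacy providers are in both arms. Nurses appear in the article as navigators and, under post-trial care, in this sentence: "The study provides comprehensive PrEP training to the pharmacy providers and nurses delivering PrEP". Control pharmacies are defined by not receiving a navigator, and their delivery is described with a provider and a remote clinician. The plain reading is provider only in control, and provider plus nurse in the navigator arm. This is an inference, though a strong one, since the sentence does not say nurse navigators.

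**Step 2: the plan's own figure.** The sample size section gives 90% power from 10 clusters per arm, m = 95, p0 = 0.30, p1 = 0.45, k = 0.05 and two-sided α = 0.05. The usual formula is

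c = 1 + (1.96 + 1.2816)² × [p0(1−p0)/m + p1(1−p1)/m + k²(p0² + p1²)] / (p1−p0)²

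With m = 95: c = 1 + 10.508 × 0.005547 / 0.0225 = 3.6 clusters per arm. With m = 80.75 (95 × 0.85): c = 4.0. Power with 10 clusters is above 99.9%, so the 90% is not reproduced; it would correspond to k of about 0.22. The present point does not rest on that figure, but k matters in step 4, so both values are used there.

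**Step 3: size of a retention artefact.** Let r be retention and u the proportion using PrEP among retained women. With missing scored as failure, observed persistence = r × u. The documents give only 15% attrition overall, so retention by arm is assumed. Take no true effect (u equal in both arms), control r = 0.85 and observed control persistence 0.30, so u = 0.30/0.85 = 0.353.

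| Navigator-arm retention | Observed persistence | Difference | Relative risk |
|---|---|---|---|
| 85% | 0.353 × 0.85 = 0.300 | 0 | 1.00 |
| 90% | 0.353 × 0.90 = 0.318 | +1.8 points | 1.06 |
| 95% | 0.353 × 0.95 = 0.335 | +3.5 points | 1.12 |

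If the 30% is instead persistence among retained women (u = 0.30), the differences are +1.5 and +3.0 points.

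The artefact equals the retention gap times u among the extra women retained. It needs those women to use PrEP at the same rate as the others seen. If all of them had stopped, it would be zero.

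**Step 4: effect on the test.** SE² = [p0(1−p0)/95 + p1(1−p1)/95 + k²(p0² + p1²)]/10, with a normal test at ±1.96.

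| Retention | Difference | SE at k = 0.05 | Rejection | SE at k = 0.22 | Rejection |
|---|---|---|---|---|---|
| 85% v 85% | 0 | 0.0221 | 5% | 0.0362 | 5% |
| 85% v 90% | 0.0176 | 0.0223 | 12% | 0.0371 | 8% |
| 85% v 95% | 0.0353 | 0.0225 | 35% | 0.0379 | 15% |

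The same mechanism applies to the hair-based adherence outcome, where no sample at 10 months means failure, and to initiation at 1 month if a missed 30-day visit is handled under the general rule.

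**The case against.** The strongest reply is that the trial tests a package. The aim is stated as the "additional benefit (i.e., effect) of stationing a nurse navigator at retail pharmacies", so whatever a stationed nurse does, reminding included, follows from allocation and is part of the effect. Refill memory is already a counselling topic. This stands for the first consequence: if nurse reminders belong to the package, a resulting change in PrEP use is effect and not confounding. The article, however, files reminders under retention and omits them from the intervention. The reply also does not reach the second consequence, because a retention gap scored as failure creates a difference with no change in PrEP use.

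A second reply is that call counts and scripts belong in operating procedures that a condensed article need not print. That is fair, and their absence is not the complaint. The complaint concerns what is printed: who makes the reminders.

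Stronger readings are tempting but not supported:

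- **That reminders will differ in number or mode.** The text does not say so, and control women are reminded too. They can differ, and nothing stated prevents it.
- **That one arm alone is under pressure to please the caller.** Providers counsel on adherence in both arms, study staff administer the questionnaires, and the third primary outcome is a hair drug level.
- **That reminders alone would add some given number of points to true PrEP use.** No figure in the documents supports one.

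**Conclusion.** The point holds in a limited form and is worth acting on. On a plain reading, the staff who make study reminders differ by arm, reminders sit outside the described intervention, and the missing-data rule converts any retention gap into an apparent effect in favour of the better-retained arm. For assumed gaps of 5 to 10 points, the artefact is about 1.8 to 3.5 points against a design difference of 15. This would not by itself produce the effect the trial is designed to detect, but it could make a null or small effect look real: false rejection of about 12% to 35% at the plan's k of 0.05, or about 8% to 15% at k of 0.22.

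These sizes rest on assumed retention by arm, equal PrEP use among retained women, and extra retained women who resemble the rest. The documents do not show that reminding or retention is in fact unequal.

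**What to change.** - Send study-visit reminders on one identical schedule and script in both arms (same mode, same number of attempts), from existing study staff or by automated message.
- If navigators make further contacts, list these in the intervention description and log them as intervention.
- Report reminder contacts and retention at each visit by arm.
- Add a sensitivity analysis of the three primary outcomes that does not count missing as failure, for example one that varies the assumed use among missing women separately by arm.

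The cost is a change of sender, a short operating procedure and a contact log. Pharmacy follow-up becomes somewhat less naturalistic. Recruitment began in May 2023, so a change made part-way would leave women followed under two procedures; its date should be recorded and applied to all pharmacies at once. If follow-up is already complete, reminder contacts cannot be recreated, but retention by arm and the sensitivity analysis still can be reported.

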### Data management 

Research Electronic Data Capture (REDCap) hosted at University of Washington’s Institute of Translational Health Sciences is used for data collection and management. De-identified data will be uploaded to a secure server on a REDCap server accessible only to data managers, study coordinators, and principal investigators. REDCap’s capability for offline data entry will be used with password-protected tablets, with later use of a secure internet connection to upload data to local servers and a secure server. No participant personal identifiers will be entered in the REDCap database. All local databases will be secured with password-protected access systems. Forms, lists, logbooks, appointment books, and any other listings that link participant ID numbers to other identifying information will be stored in a separate, locked file in an area with limited access.

### Confidentiality 

Every effort will be made to protect participant privacy and confidentiality to the extent possible. Personal identifying information will be retained at the local study site and not forwarded to the University of Washington Coordinating Center. The site will use a standard operating procedure for confidentiality protection that reflects the input of study staff and community representatives to identify potential confidentiality issues and strategies to address them. All study-related information will be stored securely at the study site. All participant information will be stored in areas with limited access. Data collection, administrative forms, laboratory specimens, and other reports will be identified only by a coded number to maintain participant confidentiality. All records that contain names or other personal identifiers, such as locator forms and informed consent forms, will be stored separately from study records identified by code number. All local databases will be secured with password-protected access systems. Forms, lists, logbooks, appointment books, and any other listings that link participant ID numbers to other identifying information will be stored in a separate, locked file in an area with limited access. Only study staff will have access to electronic data via an encrypted server.

### Plans for collection, laboratory evaluation, and storage of biological specimens for genetic or molecular analysis in this trial/future use

Hair samples (~ 50 strands) will be collected from all participants at every follow-up visit to objectively assess PrEP use and longitudinal analyses of PrEP use patterns. A strong correlation between dosing frequency and ARV levels in the hair has been demonstrated [20] [1], and significant correlations were seen between the hair, plasma, peripheral blood mononuclear cells (PBMCs), and red blood cell (in dried blood spots, DBS) levels of PrEP drugs or metabolites [2, 3]. We will analyze hair samples to evaluate either TFV levels following daily oral PrEP use and DPV levels following DPV-VR use.

## Statistical methods

### Statistical methods for primary and secondary outcomes 

We will conduct an intention-to-treat analysis with the primary exposure of randomization arm (pharmacy-based PrEP delivery with nurse navigators vs. standard pharmacy-based PrEP delivery without nurse navigators) to test the hypotheses that incorporating nurse navigators within a pharmacy-based PrEP delivery model will improve PrEP initiation, persistence, and adherence among AGYW seeking contraception at retail pharmacies.

For analyses of our primary outcomes, we will use a log-binomial regression model to estimate relative risks and 95% CI. We will include any imbalanced baseline demographic, clinical, or behavioral characteristics between arms as independent variables in an adjusted model. If primary outcome data are missing or in cases of loss to follow-up, we will assume PrEP discontinuation/nonadherence to fit the most conservative models.

Secondary outcome analyses will include PrEP method selection, predictors of non-adherence, and STI incidence and cofactors. For data analysis approaches, we will use log-binomial regression with robust standard errors for the former two and Anderson-Gill survival analysis for the later. Exploratory analyses will include HIV incidence, quality of care, and contraceptive method mixed by randomization arms (Table 1). We will use survival analysis, generalized estimating equation models with logistic link, and robust standard errors and log binomial regression respectively.

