### Sample size 

To account for between-cluster variability, sample size calculations incorporated the coefficient of variation between pharmacies (*k*) [25, 26]. Assuming each cluster enrolls 95 (accounting for 15% attrition) AGYW and that 30% of participants achieve the primary outcome of PrEP persistence at 10 months (31) in the standard pharmacy PrEP model arm (control arm) arm with a coefficient of variation between clinics (*k*) of 0.05, 10 clusters per arm will give 90% power to detect a 15% absolute difference in proportions and a two-sided test with *α* = 0.05. Typical (*k*) values are 0.15 to 0.5 for rare binary outcomes and 0 to 0.05 for non-rare outcomes [25, 26]. Assuming 15% attrition, will enroll a final sample of 1900 ANC attendees at 20 sites (95 women per site; 950 women per arm).

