### Methods for additional analyses (e.g., subgroup analyses) 

Subgroup analyses will involve data from all AGYW at the enrollment visit to evaluate the effect of STI testing on PrEP initiation. We will also evaluate the association between offering STI testing at PrEP initiation and time-to-discontinuation using Cox proportional hazards models. We will have sufficient power to detect differences in the frequency of PrEP persistence of 14% or 60% between AGYW offered and not offered STI testing, assuming a 2-sided test with alpha = 0.05 and 80% power (*β* = 0.20). All models will use robust standard errors.

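### The primary-outcome model is stated with no allowance for pharmacy clustering, so followed as written its intervals are too narrow: slightly for persistence at the plan's own k, more for initiation or a larger k

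*Protocol article*

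**What the plan says.** The Trial design section makes the pharmacy the randomized unit: "20 retail pharmacies offering standard PrEP delivery are randomized 1:1". Sequence generation adds that randomization was restricted on the volume of young women clients and stratified by sub-county, and that assignments were drawn from a bag within each of 10 groups.

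The Sample size section allows for clustering: "To account for between-cluster variability, sample size calculations incorporated the coefficient of variation between pharmacies", "with a coefficient of variation between clinics (*k*) of 0.05". It also gives the range it regards as typical: "values are 0.15 to 0.5 for rare binary outcomes and 0 to 0.05 for non-rare outcomes".

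Statistical methods for primary and secondary outcomes then fixes the analysis of initiation, persistence and adherence: "For analyses of our primary outcomes, we will use a log-binomial regression model to estimate relative risks and 95% CI". Rules for covariates and missing outcomes follow, but nothing on pharmacy. For PrEP method selection and predictors of non-adherence the same section says "we will use log-binomial regression with robust standard errors for the former two", and it lists GEE and robust errors among the exploratory methods. The subgroup section, after a Cox model for STI testing, ends: "All models will use robust standard errors". No sentence in the article says that any analysis accounts for pharmacy.

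**The concern.** Women recruited at one pharmacy share a provider, a neighbourhood and, in one arm, a nurse navigator. Their outcomes are likely to be correlated, and the arm effect is estimated from 10 pharmacies against 10. A plain log-binomial model takes its standard error as if about 1900 women had been randomized one by one. If the intraclass correlation (ICC) is above zero, that standard error is too small and the test rejects a true null more often than 5% of the time. The error favours declaring nurse navigators effective, and the article says its results are meant to inform policy makers.

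The text is also uneven. Design and sample size recognize clustering, and some secondary and exploratory analyses get robust errors or GEE, while the primary sentence has none of these.

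**Working it through.** **Inputs from the protocol.** 10 pharmacies per arm, 95 women each, persistence 30% in control, 15-point difference, k = 0.05, two-sided alpha 0.05 (Sample size). Missing primary outcomes count as failures, so cluster size m stays at 95 (Statistical methods). Pilot initiation 85% (Background and rationale).

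**The plan's own figure.** The unmatched cluster formula for clusters per arm is c = 1 + (1.96 + 1.2816)² × [p0(1−p0)/m + p1(1−p1)/m + k²(p0² + p1²)] / (p1−p0)².

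- Bracket: (0.21 + 0.2475)/95 + 0.0025 × (0.09 + 0.2025) = 0.00482 + 0.00073 = 0.00555.
- c = 1 + 10.51 × 0.00555/0.0225 = 3.6, so about 4 clusters per arm give 90% power.
- With 10 per arm, power is above 99.9%, not the stated 90%. Reaching 90% would take k of about 0.22.

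That mismatch is a separate matter. It is not used here as evidence of the true k.

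**Type I error if clustering is ignored.** The between-pharmacy variance is k²p², so:

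- ICC = k²p/(1−p)
- design effect DE = 1 + (m−1) × ICC
- actual two-sided error = 2[1 − Φ(1.96/√DE)]

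Persistence at the stated k: ICC = 0.0025 × 0.30/0.70 = 0.0011; DE = 1 + 94 × 0.00107 = 1.10; 1.96/1.049 = 1.868; error 6.2%. A correct interval would be 1.05 times as wide.

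Initiation at the same k, assuming 85%: ICC = 0.0025 × 0.85/0.15 = 0.0142; DE = 1 + 94 × 0.01417 = 2.33; 1.96/1.527 = 1.284; error 19.9%. A correct interval would be 1.53 times as wide.

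| Outcome | k | DE | Error, formula | Error, simulation |
|---|---|---|---|---|
| Persistence 30% | 0.05 (stated) | 1.10 | 6.2% | 6.2% |
| Persistence 30% | 0.10 (assumed) | 1.40 | 9.8% | not run |
| Persistence 30% | 0.15 (assumed) | 1.91 | 15.6% | 15.8% |
| Persistence 30% | 0.25 (assumed) | 3.52 | 29.6% | 29.5% |
| Initiation 85% (assumed) | 0.05 (stated) | 2.33 | 19.9% | 19.8% |

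The simulation used 20,000 beta-binomial trials per row, with 10 + 10 clusters of 95. With m = 81 (15% lost) the first and last rows become 6.0% and 18.0%.

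The two outcomes differ because k is relative to the rate. At k = 0.05 the standard deviation of true pharmacy rates is 0.05 × 30 = 1.5 points for persistence, but 0.05 × 85 = 4.25 points for initiation, where the binomial variance is also smaller.

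**Would robust errors cure it?** A sandwich variance not clustered on pharmacy still treats the women as independent. In the same simulations at 30%, an uncorrected pharmacy-clustered sandwich with a normal reference gave 7.6% to 8.0%. A t-test on pharmacy-level results with 18 degrees of freedom gave about 5%.

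**The case against.** The article condenses a fuller protocol, and its Interim analyses section refers to a statistical analysis plan that is not shown. Naming a regression family does not say that women will be treated as independent, and the choice of variance estimator and small-sample correction is ordinary analysis-plan content. The closing sentence of the subgroup section can be read as covering every model. All this stands to the extent that one cannot say the trial will be analysed without regard to pharmacy. It does not remove the point. The article chose to fix the primary model, effect measure, covariate rule and missing-data rule, and it attached robust errors elsewhere but not there. Even the generous reading of the later sentence leaves the clustering level unnamed.

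On size, the objection is stronger. At the plan's own k the excess for persistence is about one percentage point. The k values from 0.10 upward are not the plan's: it gives 0 to 0.05 for non-rare outcomes, and 30% is not rare. The 20% for initiation rests on a two-pharmacy pilot in which nurse navigators were present.

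The figures also ignore the draw within 10 groups, which for 20 pharmacies suggests pairs. If grouping removed half the between-pharmacy variance (an assumption), DE − 1 would halve. The error would be about 5.6% for persistence at k = 0.05 (DE 1.05), 10% at k = 0.15 (DE 1.45) and 13% for initiation (DE 1.67). That reduces the inflation without removing it.

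**Conclusion.** The point holds as a defect in the stated primary analysis. The sentence omits the randomized unit, conflicts with the allowance made in the sample size, and is not repaired by the robust-error sentence. Followed as written, it gives a type I error of about 6.2% for persistence at k = 0.05, and about 20% for initiation at the same k if the pilot's 85% carries over. For persistence it gives about 10%, 16% and 30% at assumed k of 0.10, 0.15 and 0.25. All of these are before any gain from the restricted randomization.

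A reader might infer that the false-positive risk is well above 5% for every primary outcome. The document does not support that: with its own k and persistence rate the inflation is slight, and the large values need either a high outcome rate or a k that it does not assume. A reader might also take the k of about 0.22 behind 90% power as the true value, but it may only reflect an error elsewhere in that calculation. The true between-pharmacy variation is unknown before the data, which is why the analysis should not depend on its being negligible.

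**What to change.** State in Statistical methods that all primary arm comparisons, and the secondary and exploratory ones, account for pharmacy as the cluster and for the groups or strata used in randomization, by a method valid with 20 clusters. Either of these would serve:

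- log-link GEE (modified Poisson) clustered on pharmacy, with a small-sample corrected variance and a t reference;
- a cluster-level analysis with degrees of freedom that match the randomization: 20 − 2 = 18 if unmatched, 10 − 1 = 9 if the 10 groups are pairs.

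Say which of these two structures the draw produced. In the subgroup section, say whether the robust-error sentence covers the primary models and that the clustering level is the pharmacy. If the analysis plan already says this, bring the protocol wording into line with it.

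The cost is wording only: no new data and no change to recruitment or follow-up. Intervals become somewhat wider, by about 5% for persistence at the stated k before any small-sample correction.
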